## Methods

We will use a double blind randomized parallel design. Patients will be invited to the study by sending a letter from the perinatal clinic office inviting them to contact us. Consent will be handed to the parents at the beginning of the study. Subject randomization will be carried out using a computer generated random numbers. Medications and placebo will be kept locked in a cabinet in the clinic area, one of the clinic nurses will be responsible for dispensing the medication or placebo. The medication or placebo will be taken twice daily, at 08:00 and 20:00. The Placebo will have the same taste, shape and color of the study drug. There will be a run in period for 1 week before the study, for teaching the patients, and checking proper technique, and filling out the Child Health Questionnaire (CHQ). In the first visit, informed consent filled, inclusion and exclusion criteria will be obtained. Medical and surgical history, physical exam, inhalation and pulmonary function technique will be done. We will review the daily diary, and prepare the placebo for all patients in the run in period. One week after the run in period, randomization carried out and patients entered into the study. Phone calls will be carried out every two weeks to optimize compliance. After six weeks of treatment, CHQ will be filled. Forced expiratory volume at 1 second (FEV1) (for children older than 6 years of age) and respiratory system resistance at 5 Hz frequencies will be measured.

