The Study of a patient should be delayed six weeks if developed a viral respiratory illness. Bronchodilators should not be used on the day of the study visit (at least 24 hours for long acting, 6 hours for short acting). Neonatal variables to be collected from medical records: gender, birth weight, birth length, head circumference, gestational age, neonatal treatment, total days on oxygen, maximal FiO2, days on CPAP, days on IPPV, use of steroids (how much and how long), and the use of surfactant. Maternal data: parity, living offspring's, and smoking days during pregnancy. Skin prick testing for the 10 common allergens will be done at the start of the study. Atopy will be defined by one or more positive reactions (3 mm wheal) to 10 common aeroallergens. Parents will fill out daily symptom scores. Social and environmental data to be collected are smoking habits, pets, family history of asthma and asthma in the child. Methacholine challenge testing will be done in the start of the study to define those patients with airway hyper reactivity, which might be a sensitive indicator of response to steroids [6,7]. Respiratory function will be measured using Spirometry (FEV1) and Impulse Oscillometry (RS @ 5 Hz). Quality of life will be measured using the CHQ. Treatment group will receive QVAR 100 mcg 2 puffs twice daily; placebo will be given to the other arm for 6 weeks, after which the respiratory function and quality of life will be measured.

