### Primary outcome measures

Improvement in respiratory system resistance at 5 Hz frequency measured by impulse oscillometry after 6 weeks of inhaled corticosteroids in CLD.

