### Statistical consideration

The required number of patients was estimated as n = 74 (37 in each group) and to allow 10% dropout we need 82 patients. The sample size estimation was based on a type I error rate of = .05 and a type II error rate of = 0.20. The improvement in airway resistance at 5 HZ as primary end point was expected to be 15% for the treatment group. The coefficient variation for the impulse oscillometry measurement is 10%. The primary statistical analysis of efficacy data is based on the intention-to-treat patients, who were randomly assigned to treatment and received at least one dose of medication. Baseline characteristics will be compared using descriptive statistics including confidence intervals. Imbalance between the groups on key variables, which might influence the observed outcome, will indicate that an adjusted analysis is necessary using these variables. The differences between airway resistance at 5 HZ response will be tested with a 2-tailed paired test on a significance level of = .05. Analysis of FEV1 improvement will be performed by two-tailed T test (= .05). All tests, except those for CHQ, will be done by SSPS procedures. For CHQ analysis, the differences of sum scores at week 6 after treatment to baseline will be tested by Wilcoxon rank sum test using StatXa.

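### The primary endpoint is assigned a paired test, which cannot compare drug with placebo in a trial of two independent parallel arms

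*Protocol article*

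**What the plan says.** The Methods of the protocol article fix the design: "We will use a double blind randomized parallel design". For the control group they state that "placebo will be given to the other arm for 6 weeks". No crossover, matching or pairing of children across arms is described.

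The primary outcome is given as "Improvement in respiratory system resistance at 5 Hz frequency measured by impulse oscillometry after 6 weeks of inhaled corticosteroids in CLD". The Statistical consideration section sizes the trial by group: "The required number of patients was estimated as n = 74 (37 in each group) and to allow 10% dropout we need 82 patients". The error rates are "based on a type I error rate of = .05 and a type II error rate of = 0.20", and the expected effect is worded for one arm: "The improvement in airway resistance at 5 HZ as primary end point was expected to be 15% for the treatment group".

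The same section then names the primary test: "The differences between airway resistance at 5 HZ response will be tested with a 2-tailed paired test", at the 0.05 level. For the secondary endpoints it names a two-tailed t test for FEV1, not labelled paired or unpaired, and a Wilcoxon rank sum test for the change in Child Health Questionnaire (CHQ) scores from baseline to week 6. An adjusted analysis is foreseen only if the groups turn out imbalanced on key variables, and no model is named for it.

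**The concern.** A paired test needs pairs. With different children in each arm and no matching, none exist across arms. Those that do exist are repeated measurements on one child: baseline against week 6, or before against after salbutamol, since the Methods record resistance at both moments. Neither contrast is drug against placebo.

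The change from baseline within the active arm contains the drug effect plus anything that would also have happened on placebo, such as regression to the mean, learning of the manoeuvre and natural course. The placebo arm is there to remove these. A test that does not use it can declare efficacy when the two arms improve by the same amount, and its 5% error rate then does not apply to the question the trial was randomised to answer.

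This is not a detail left to a fuller document. The article names the test for its primary endpoint, and the named test does not fit its own design.

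**Working it through.** **1. Test against design.**

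| Item | Where stated | Implies |
|---|---|---|
| Randomised parallel arms, placebo in the other arm | Methods | Independent groups |
| 37 in each group | Statistical consideration | Independent groups |
| Rank sum test on CHQ change scores | Statistical consideration | Independent groups |
| Paired test on resistance at 5 Hz | Statistical consideration | Pairs, which exist only within a child |

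The primary test is the entry that does not fit.

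**2. Does the plan's sample size show which test was meant?** Inputs from the Statistical consideration section: two-sided alpha 0.05, power 80%, improvement 15%, and "The coefficient variation for the impulse oscillometry measurement is 10" percent. The normal quantiles sum to 1.960 + 0.842 = 2.802.

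- Two-sample formula, n per group = 2 × (2.802 × SD / 15)². SD 10 gives 6.98, so 7. SD 14.1 (10 × √2, if the 10% is measurement error at both visits) gives 13.95, so 14.
- Paired formula, n = (2.802 × SD / 15)². SD 10 gives 3.49, so 4 pairs. SD 14.1 gives 6.98, so 7 pairs.

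Neither gives 37. The two-sample formula reaches 37 per group only at an SD of 15 / (2.802 × √(2/37)) = 23.0, or 22.7 with the exact t distribution (power 80.07%). No such SD is stated. The sample size therefore does not settle which test was intended. That it cannot be reproduced is a separate matter, on which this point does not depend.

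**3. What the literal test would do.** Suppose the drug has no effect and both arms improve by c points. The active-arm paired t test with n = 37 has 36 degrees of freedom, critical value 2.028 and noncentrality c × √37 / SD, where √37 = 6.083. The values of c are assumed. So are the SDs of change: 10 takes the stated coefficient directly, 14.1 takes it as measurement error at two visits, and 22.7 is back-solved from 37 per group.

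| Shared improvement c | SD of change | Noncentrality | Active-arm paired test significant |
|---|---|---|---|
| 0 | any | 0 | 5% |
| 5 | 10 | 3.04 | 84% |
| 5 | 14.1 | 2.15 | 55% |
| 5 | 22.7 | 1.34 | 26% |
| 7.5 | 10 | 4.56 | 99% |
| 7.5 | 14.1 | 3.23 | 88% |
| 7.5 | 22.7 | 2.01 | 50% |

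**4. What a between-group test would do.** A shared change cancels in the difference between arms. In 40,000 simulated trials at SD 14.1, the two-sample t test rejected in 4.8% with no shared change and in 5.0% with a shared 5-point change.

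**The case against.** The strongest reply is that a between-group comparison was meant all along and that the word paired is a slip for unpaired. The section counts patients per group, defines an intention-to-treat set of randomised patients, and foresees adjustment when the groups are imbalanced, which would have no purpose in a within-arm test. The sentence itself speaks of differences between responses. This reading is plausible and should be allowed. But the text does not say it, and the conditional, unnamed adjusted analysis does not supply the missing primary test. A slip in the only stated primary test still has to be corrected.

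A reader might infer more than the document supports:

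- **That the sponsor planned to discard the placebo comparison.** This is the literal reading, not a demonstrated intention. The wording of the primary outcome does not prove it: the CHQ outcome is phrased in the same way, as improvement after treatment, and still gets an independent-groups test.
- **That baseline against week 6 is the only possible pairing.** Before and after salbutamol is a second one, and the word response could refer to either.
- **That the primary endpoint alone has the wrong test.** The FEV1 test is not labelled paired or unpaired, so only the contrast with CHQ is secure.
- **That the trial has a false-positive rate of 25% or more.** The rates above depend on an assumed shared improvement. A further figure of up to 25%, for a significant active arm with a non-significant placebo arm, also needs a decision rule that the protocol never states.

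The one-week placebo run-in with technique teaching, the practice trials and the six-week delay after viral illness should also reduce shared drift. They do not remove it, and they do not make a paired test valid for independent groups.

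**Conclusion.** The point stands in this form: the named primary test contradicts the parallel design, cannot estimate drug against placebo, and is out of line with the independent-groups test given to CHQ. That conclusion needs no assumption.

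The size of the consequence does. With 37 per arm, no drug effect and a shared 5-point improvement, the literal test would be significant in roughly 26% to 84% of trials over the SDs considered. With no shared change there is no inflation. These figures illustrate the risk and do not estimate this trial's error rate. Because the sentence governs the only primary efficacy test and its literal reading can change the trial's conclusion, it must be corrected whether it is a slip or a real choice.

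**What to change.** Replace the sentence on the primary test with a two-sided between-group comparison at alpha 0.05 of the change in resistance at 5 Hz from baseline to week 6. A two-sample t test on change is enough. ANCOVA of the week-6 value on treatment group and baseline value is preferable. Report the between-group difference with its 95% confidence interval.

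A log scale, naming the pre-salbutamol value as the one analysed, and rewording the primary outcome relative to placebo are useful but optional.

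The cost is wording only: no further patients, visits or data are needed.

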**Methods:**

Our primary hypothesis is that using inhaled steroids; Beclomethasone Dipropionate (QVAR) 100 mcg 2 puffs 2 times a day for 6 weeks will improve the respiratory system resistance and the quality of life in children with CLD.

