### Secondary outcome measures

Improvement in Quality of life system score using Child Health Questionnaire (CHQ) and FEV1 response to bronchodilators (Salbutamol) after inhaled corticosteroids treatment for 6 weeks in children with CLD.

The inclusion criteria: children between 3 and 9 years of age with a history of CLD with the following criteria.

1. Premature birth at 36 weeks gestation or less.

2. Clinical and radiological diagnosis of CLD. Patient charts will be reviewed and the x-rays will be reviewed, even if there is no x-ray findings patients will be included if they fulfil the other criteria.

3. Requirement of supplemental oxygen to maintain saturation of 90%, for at least 36 wk corrected gestation.

The exclusion criteria:

1. Cardiovascular disease other than PDA (Patent Ductus Arteriosus)

2. Those with severe neurological disease, developmental delay. Oxygen requirement for respiratory diagnosis other than CLD e.g. congenital diaphragmatic hernia and aspiration. An inability to perform spirometry or IOS, or noncompliance with therapy and those with pneumonia.

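### The CHQ change score is compared without conditioning on baseline CHQ; pre-specifying a baseline-adjusted analysis would probably gain power on this secondary outcome

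*Protocol article*

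**What the plan says.** All places are in the Protocol article.

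- **Test.** Statistical consideration: "the differences of sum scores at week 6 after treatment to baseline will be tested by Wilcoxon rank sum test". The comparison is between arms, on week-6 score minus baseline score.
- **Data.** Under Methods, the CHQ is first completed in the one-week run-in, before randomisation. The second completion is also fixed there: "After six weeks of treatment, CHQ will be filled".
- **Adjustment.** Statistical consideration has one rule: "Imbalance between the groups on key variables, which might influence the observed outcome, will indicate that an adjusted analysis is necessary using these variables". The key variables are not named, and baseline CHQ is not mentioned among them.
- **Status.** Secondary outcome measures lists the CHQ score. The Methods paragraph of the Abstract puts it beside resistance, in a hypothesis that treatment "will improve the respiratory system resistance and the quality of life in children with CLD", but the formal Primary hypothesis and Primary outcome measures name resistance only.
- **Size.** The 74 children (37 per arm) are justified on resistance at 5 Hz. No effect, SD, correlation or power is given for CHQ.

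**The concern.** Subtracting baseline fixes the slope of week-6 score on baseline score at 1. If the true slope is smaller, as it is with equal variances and a correlation below 1, the change score carries more baseline noise than it needs to. Estimating the slope, by entering baseline CHQ as a covariate, removes that noise and uses data the trial already collects.

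The adjustment rule does not fill the gap. It is triggered by observed imbalance, whereas the precision gain exists even when the arms are perfectly balanced. It also leaves the choice of covariates until the data have been seen.

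At stake is power for a secondary outcome on which the trial was not sized, so a real quality-of-life benefit is more easily missed than it need be.

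**Working it through.** **Inputs.** From the article: 37 per arm, two assessments (run-in and week 6), rank-sum test on change. The 5% level is stated for the other tests; two-sided 5% is assumed for CHQ. Also assumed, because the article gives none: the baseline-to-week-6 correlation ρ, equal SD at both times, the effect size and the score distribution. There is no planned CHQ figure to reproduce.

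**Step 1: variance against mean change.** With score SD σ, a change has variance 2σ²(1−ρ), and a week-6 score adjusted for baseline has variance σ²(1−ρ²). The ratio is (1−ρ²)/(2(1−ρ)) = (1+ρ)/2, that is 0.70, 0.75, 0.80, 0.85 and 0.95 at ρ = 0.4, 0.5, 0.6, 0.7 and 0.9. The comparator here is a t test on mean change, not the planned rank-sum test.

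**Step 2: formula power against the planned test, normal data.** The rank-sum test multiplies the change-score variance by about π/3. At ρ = 0.5, with a 0.5σ benefit:

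- Rank-sum on change: SE = √(2/37 × 1 × π/3) = 0.238; 0.5/0.238 − 1.96 = 0.14; power about 56%.
- ANCOVA: SE = √(2/37 × 0.75) = 0.201; 0.5/0.201 − 1.96 = 0.52; power about 70%.

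**Step 3: simulation, normal data, 0.5 SD benefit, 37 per arm, 4,000 trials per setting.** Quade is the rank-based ANCOVA.

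| ρ | Rank-sum on change | ANCOVA | Quade | Gain, ANCOVA / Quade (points) |
|---|---|---|---|---|
| 0.4 | 45% | 62% | 60% | 17 / 15 |
| 0.5 | 54% | 68% | 66% | 14 / 12 |
| 0.6 | 63% | 75% | 72% | 12 / 9 |
| 0.7 | 75% | 84% | 80% | 9 / 5 |

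A separate run of 3,000 trials agreed within simulation error; at ρ = 0.7 its gains were 8 and 4 points. With no treatment effect and ρ = 0.5, the rejection rates were 5.3%, 5.5% and 5.3%, so all three tests hold their level.

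**Step 4: wider range of ρ, and skewed errors.** Here the effect is set so that a t test on change has 80% power by formula: 0.651σ√(2(1−ρ)), or 0.77, 0.65, 0.50 and 0.29 SD at ρ = 0.3, 0.5, 0.7 and 0.9. Entries are rank-sum on change / ANCOVA / Quade.

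| ρ | Normal errors | Exponential errors |
|---|---|---|
| 0.3 | 76.5 / 92.4 / 90.9% | 85.2 / 91.4 / 98.6% |
| 0.5 | 76.3 / 88.2 / 86.1% | 88.3 / 88.0 / 95.8% |
| 0.7 | 75.6 / 84.2 / 79.8% | 91.0 / 84.2 / 89.0% |
| 0.9 | 77.2 / 80.7 / 72.8% | 93.8 / 80.2 / 77.6% |

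At ρ = 0.9 with normal data, ANCOVA gains about 3.5 points and Quade loses about 4. With exponential errors, the rank-sum test ties with linear ANCOVA at ρ = 0.5 and beats it by 7 points at 0.7 and 14 at 0.9. Quade gains at 0.3 and 0.5, is 2 points behind at 0.7 and 16 behind at 0.9.

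**Step 5: two other non-normal shapes, 0.5 SD benefit** (same order of entries).

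- Scores capped at +1 SD: 45/62/63% at ρ = 0.5, 63/78/78% at 0.7, 97/99/99% at 0.9.
- Log-normal-type scores: 46/59/64%, 66/75/80% and 97/98/99%.

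In both, each adjusted analysis beats the planned test.

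**The case against.** The strongest defence is that the plan is valid and looks deliberate. FEV1 gets a t test, while CHQ is set apart with a nonparametric test and its own software. That fits a wish for robustness with a questionnaire sum score, and under strong skew and high correlation the robustness pays. This stands: the gain is conditional, and a replacement should not give up rank-based protection without thought.

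Some stronger readings are tempting but not supported:

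- *The baseline CHQ is thrown away.* It is not; it enters by subtraction. What is missing is conditioning on it.
- *The test is wrong or biased.* Under randomisation the change-score comparison is unbiased, and its simulated error rate is about 5%.
- *Adjustment is worth about 99 children instead of 74.* That figure (74/0.75 = 98.7, at ρ = 0.5) compares ANCOVA with mean change, so it does not measure the gain over the rank-sum test.
- *Adjustment wins at any correlation below 1, at no cost.* That is true of the variance in Step 1, not of power under every distribution, as Step 4 shows.
- *A primary claim is at risk.* Only an Abstract sentence links quality of life to the primary hypothesis; the formal sections make it secondary.
- *No effect size will be reported.* The article names a test. Estimates and intervals are commonly left to the full protocol or SAP, and a rank-sum test can be accompanied by a Hodges-Lehmann shift and interval.

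The imbalance rule also counts for the plan, because adjustment is not ruled out. But it is data-driven and does not pre-specify baseline CHQ.

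**Conclusion.** The point holds as an efficiency improvement on a secondary outcome. The article fixes an analysis that does not condition on an available pre-randomisation covariate.

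The gain of roughly 9 to 17 points (linear) or 4 to 15 points (rank-based) rests on normal scores, equal SDs, a 0.5 SD benefit, 37 per arm and ρ between 0.4 and 0.7. None of the distributional inputs comes from the article. The advantage shrinks towards nothing as ρ approaches 0.9. It can reverse for linear ANCOVA at ρ of 0.7 or more when errors are strongly skewed, and for the rank version at about 0.9. Low to moderate correlation favours adjustment under every shape tried, with one tie (linear ANCOVA, exponential errors, ρ = 0.5).

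**What to change.** Replace the CHQ sentence in Statistical consideration with one pre-specified baseline-adjusted main analysis. Either option answers the point:

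- ANCOVA of week-6 CHQ on arm and baseline CHQ, reporting the adjusted difference with its 95% CI; or
- rank ANCOVA (Quade) with baseline CHQ as covariate, if the rank-based robustness of the present plan is to be kept. Quade's test gives a p-value but no adjusted difference, so an estimate would have to be named separately.

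Make the choice before unblinding. Do not let a check of residuals decide between the two, since that would be an undefined, data-driven switch. Keep the rank-sum test on change as a sensitivity analysis.

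The cost is one sentence of wording and slightly more analysis work, with no new data, visits or children. The downside is a possible loss of power if scores turn out both strongly skewed and highly correlated: with exponential errors at ρ = 0.7, 2 points for the rank version and 7 for the linear one, and more at 0.9.

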## Discussion

Bronchopulmonary Dysplasia (BPD) is a chronic lung disease related to injury induced by mechanical ventilation and oxygen therapy in prematurely born infants. William Northway, a radiologist at Stanford University, described this pathology in 1967[8]. More recently the term chronic lung disease (CLD) has been used since nowadays preterm infants with birth weights between 500 and 750 grams have at least a 50 percent chance of survival at 24 weeks gestation age[9]. The clinical diagnosis of this CLD is made at one month of age in prematurely born infants who have undergone mechanical ventilation for at least one week, who have symptoms of persistent respiratory distress, are dependent on supplemental oxygen, and who have chest radiographs that show rounded radio lucent areas in the lung alternating with thinner strands of radiodensity.

The pathogenesis of CLD is believed to be multifactorial, with pulmonary oxygen toxicity and barotrauma having important roles [10]. More recently inflammatory mediators, cytokines, and proteolytic enzymes released by inflammatory cells, whose influx into the lungs is the consequence of oxygen exposure and prenatal or postnatal sepsis, were described [11]. The release of neuropeptides such as substance P from afferent nerve endings in the airways or lung parenchyma may accelerate this inflammatory cascade[12]. Coates et al found decreased expiratory flows in children 7 and 8 years old who had survived the respiratory distress syndrome, and later suggested that oxygen therapy could have been at least partly responsible for these sequelae [13]. CLD has become the most common form of chronic lung disease in infants in the United States with approximately 7000 new cases occurring each year [14].

It has been noted that infants with BPD were twice as likely to be hospitalized in the first 2 years of life compared with preterm infants without BPD [15]. But at age 7 years both groups had more cough and wheeze than the term group. Pulmonary function including lung volumes and expiratory airflow were worse in the BPD group. This group showed more evidence of gas trapping and hyperinflation and significant expiratory airflow obstruction [15]. This was confirmed by the study done by Jacob et al who compared children of BPD at 11 years old with children in a control group who were born preterm but who did not have BPD [9]. This was also supported by the findings of Coates et al who confirmed that premature birth and the development of the RDS of the newborn have been associated with long term pulmonary sequelae [13,16]. Is there any treatment available for those children?

The literature suggested that there is significant morbidity and mortality from chronic lung disease in infancy into adult and elderly ages. In a follow up study of men born during 1911–1930 whose birth weight, weight at 1 year, and childhood respiratory illnesses were recorded at that time by health visitors [17], Barker et al found that lower birth weight was associated with worse adult lung function. Bronchitis, pneumonia, or whooping cough in infancy further reduced adult lung function, they concluded that death rates from chronic obstructive disease, but not from another disease related to smoking or lung cancer fell with increasing birth weight and weight at 1 year. This was supported by the findings of Peto et al [18] in their follow up study of men whose lung function and respiratory symptoms had been assessed in adult life and showed that the risk of death from chronic obstructive airway disease was strongly correlated with the initial FEV1.

Liggins and Howie have demonstrated that the administration of a corticosteroid leads to a decreased incidence of RDS in human premature infants[19]. It is well known that inhaled and systemic steroids are used for the prevention of CLD in infancy [20]. Any pulmonary growth retardation would be expected to have an effect on the airways and result in increased airway resistance and lower flows. It was pointed out that the only major changes in airways from birth to adulthood are in their size [21]. High incidence of asthma has been noted in families of neonates in whom the RDS was complicated by CLD [22]. Other clinical studies suggest an increased incidence of airway hyper reactivity in prematurely born children [23-26]. Recurrent wheeze in childhood and readmission to hospital for bronchiolitis like illness has been observed among prematurely born children who survived the RDS [24]. Most patients with CLD also have increased airway lability and improvement in expiratory flow rates following bronchodilator inhalation suggesting that such therapy may improve pulmonary function in these children [15]. It was anticipated that the incidence of CLD would decrease after the introduction of surfactant therapy, clinical trials by Horbar and Long failed to confirm this [27,28].

So far there are no studies have been published studying the clinical response to inhaled corticosteroids in children CLD. Pulmonary function testing for these children can be done using different techniques. Pennings et al [29] used forced oscillation technique (FOT) to detect changes in airway bronchial tone of asthmatic patients, that were not detected by conventional flow volume recording. It was found that the changes of the diameter of small airways of children could be missed by routine spirometry. The apparent increase incidence of bronchiolitis in RDS survivor's points to these small airways as a source of pathology [30]. In 1956, Dubios et al described the use of FOT as a measure of total respiratory system impedance, which was non invasive and required minimal cooperation from the subject and it can be applied to infants and older children. Laberge et al used FOT to measure respiratory system resistance in 3 to 6 years old asthmatic children and they concluded that the dry powder inhaler (Turbuhaler) and the metered dose inhaler with spacer (Nebuhaler) are equally effective in administering terbutaline [31].

